### Interim analyses {21b}

No interim analyses are planned. Data collection will be terminated once the *N* = 150 is reached.

### Methods for additional analyses (e.g., subgroup analyses) {20b}

Several predefined variables (trait anxiety, SSAS, BIS/BAS, GEEE prior experience) will be subjected to subsequent moderator analyses in order to better understand specific mechanisms within the expectation and symptom change process. Equally, certain secondary outcome variables (e.g., state anxiety or perceived disability) and process measures (mood) may mediate change processes and therefore may be subject to additional mediator analyses.

### Methods in analysis to handle protocol non-adherence and any statistical methods to handle missing data {20c}

We will follow the steps outlined by the National Research Council (US) and summarized by Little and colleagues (2012) on the treatment of missing data in clinical trials [72, 73]. In order to keep the integrity of the randomization process and provide a realistic estimate of the treatment effects, we will use ITT and analyze all randomized participants regardless of treatment adherence [74]. Sensitivity analyses will be carried out to assess the impact of missing values in the outcome variable on the results and to decide on a strategy for handling missing data if necessary. If missing data is “missing-at-random” (MAR), multiple imputation is employed to model the missing data in the ITT analysis in order to retain variability in the outcome variables [72, 75–77].

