### Criteria for discontinuing or modifying allocated interventions {11b}

Participants can withdraw their written consent at any point and discontinue the study. Other reasons for discontinuation are as follows: acute suicidality and/or referral to a psychiatric hospital, a drastic increase in depressive symptoms, and adverse reactions to Buscopan. Participants are asked to provide a standardized mood rating at each study visit. In case of a very low rating (1 or 2 on a 10-point scale), further questions will be asked to assess possible suicidal tendencies and ensure the patient’s safety. Several experienced supervisors are available in the background and can be consulted on appropriate measures (e.g., referral to an in-patient clinic) in such cases.

Furthermore, some participants may be on waitlists for psychotherapy elsewhere and participate in the study to bridge the waiting time. Participants who happen to be offered a place to start psychotherapy while completing the trial also discontinue the study treatment.

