### Sample size {14}

We expect a difference of effects on the primary outcome between treatments with congruent versus incongruent contents of a priori provided treatment rationales. Based on previous research [58], we expect an effect size of Cohen’s *d* > 0.40. Our primary hypothesis comprises of the comparison of the clinical status before and after treatment using the MADRS as the primary outcome. A power of 0.90 and alpha < 0.05 and a 2 × 2 design (treatment rationale, active placebo) requires a minimum of 96 participants. Considering a 20% drop-out/treatment discontinuation, 4 groups of 30 participants are required. The 5th group (natural course) does not serve hypothesis testing. Therefore, this group is not considered in the power calculation. Based on the 5 arms in the study, a total of 150 participants are required.

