### Procedure for unblinding if needed {17b}

Unblinding is permissible if a participant becomes a drop-out or shows a marked increase in depressive symptoms and/or suicidal tendencies and is removed from the study. All participants will be debriefed orally and in writing about the aims of the study and group allocation after the study is completed. All participants are also debriefed about the congruency condition and receive both illness rationales upon study completion.

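### The missing-data strategy is to be decided after seeing its impact on the results, while patients who worsen markedly may have no post-treatment MADRS

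*Protocol article*

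**What the plan says.** The missing-data section of the protocol article {20c} promises to "analyze all randomized participants regardless of treatment adherence". It then says sensitivity analyses will "assess the impact of missing values in the outcome variable on the results and to decide on a strategy for handling missing data" if needed. Multiple imputation is used if the missing data are MAR. No method is given for the case where MAR is doubted.

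The section on discontinuing interventions {11b} gives as reasons "acute suicidality and/or referral to a psychiatric hospital, a drastic increase in depressive symptoms, and adverse reactions to Buscopan". Its last sentence, on patients offered a psychotherapy place, speaks of stopping the study treatment only. The unblinding section {17b} refers to a participant who "shows a marked increase in depressive symptoms and/or suicidal tendencies and is removed from the study", and opens with "Unblinding is permissible if a participant becomes a drop-out".

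The MADRS is rated at baseline and once after treatment (t6), by blinded clinicians {18a}. The BDI-II is taken at baseline, post-intervention and follow-up {12}. Mood is rated at each study visit {11b}, and by weekly phone call in the natural course group {11c}. A form records reasons for discontinuation {18b}. The sample-size section {14} states: "Considering a 20% drop-out/treatment discontinuation, 4 groups of 30 participants are required".

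**The concern.** Two problems meet here.

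**Order of decisions.** A sensitivity analysis should test a primary method that is already fixed. Here it helps to choose the method, after its impact on the results has been seen. The other criterion, whether MAR holds, depends on values nobody observes. The form in {18b} describes why patients left but cannot settle the question. An analysis plan written later could repair this, but the article itself states a results-dependent rule. This is therefore not a detail merely left out.

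**Source of the missing values.** A patient taken out for marked worsening is taken out for something close to the primary outcome. With a single post-baseline MADRS, that patient has no later rating unless one is sought after stopping, and the article does not say it will be. If incongruent arms worsen more, more of their poor outcomes go unseen, and an imputation that does not know about the worsening fills in values that are too good. The baseline-adjusted mixed model in {20a} also relies on MAR, so it offers no protection.

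At stake are the size of the congruence effect and the credibility of a primary result whose missing-data method was not fixed beforehand.

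**Working it through.** **1. The plan's own figure.** Section {14}: "we expect an effect size of Cohen’s *d* > 0.40" and "A power of 0.90 and alpha < 0.05 and a 2 × 2 design (treatment rationale, active placebo) requires a minimum of 96 participants". For a repeated-measures group-by-time test with 4 groups, 2 occasions, f = d/2 = 0.20 and an assumed correlation r = 0.5 (not in the article):

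- λ = N f² m/(1 − r) = 96 × 0.04 × 2/0.5 = 15.36, with 3 and 92 degrees of freedom; power = 0.912.
- Inflation: 96/(1 − 0.20) = 120 = 4 × 30.

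The figure reproduces under that assumption. The plan thus budgets 120 − 96 = 24 of 120 patients as lost to drop-out or discontinuation. This point does not concern N; the 24 only caps the assumed share below.

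**2. Set-up for the bias check.** From the article: 60 congruent against 60 incongruent, true difference 0.40 SD, loss of at most 20%. Assumed: r = 0.5; outcomes in SD units; one removal rule for all arms; no average improvement in the incongruent arms.

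With Y post-treatment and B baseline MADRS, the change Y − B has SD √(2 − 2r) = 1. A patient is removed when the change exceeds t, where overall removal p satisfies

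½[1 − Φ(t)] + ½[1 − Φ(t + 0.40)] = p.

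- p = 0.05: t = 1.48; removal about 7% incongruent, 3% congruent.
- p = 0.10: t = 1.11; about 13% and 7%.
- p = 0.20: t = 0.66; about 25% and 14 to 15%.

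**3. Imputation from arm and baseline MADRS only** (4,000 simulated trials per row, 10 imputations, baseline-adjusted comparison):

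| Missing | Estimate (true 0.40) | Power |
|---|---|---|
| none | 0.40 | 0.70 |
| 20% completely at random | 0.40 | 0.59 |
| 5% removed for worsening | 0.35 | 0.62 |
| 10% removed for worsening | 0.31 | 0.53 |
| 20% removed for worsening | 0.26 | 0.43 |

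The shortfalls are 0.05, 0.09 and 0.14 SD, or 13%, 23% and 35% of 0.40. Complete-case estimates agree to within 0.001. At 20%, loss of data alone takes power from 0.70 to 0.59; outcome-related removal accounts for the rest. With no true effect and equal removal, the average estimate is 0.00 and each single method keeps about 5% type I error.

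**4. Adding mood ratings to the imputation** (assumed mood–outcome correlation 0.7). What happens depends on what triggers removal:

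| Removed | Trigger: MADRS change; baseline only | Trigger: MADRS change; mood added | Trigger: recorded mood; mood added |
|---|---|---|---|
| 5% | 0.34 | 0.37 | about 0.40 |
| 10% | 0.31 | 0.34 | about 0.40 |
| 20% | 0.26 | 0.30 to 0.31 | about 0.40 |

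The 0.34 here and 0.35 in step 3 are the same quantity apart from simulation error. If removal follows the recorded mood but mood is left out of the model, the estimate at 20% is 0.33. So the mood ratings can remove nearly all of the bias, or only part of it.

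**5. Choosing the method by its result.** With no true effect and 20% missing, taking the most favourable of complete case, baseline carried forward and multiple imputation gives a type I error of 6.2 to 6.6% instead of 5%. This illustrates the direction; the article does not list these three candidates.

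**6. The three sections side by side.** {11b} is headed as a rule about interventions and in one place stops treatment only; {17b} has worsening patients leave the study; {20c} analyses everyone randomised. They can be reconciled, since imputation can include a patient with no t6 rating. But they do not say whether that rating is attempted.

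**The case against.** The strongest case on the other side has four parts.

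- **Missingness may be MAR.** Mood is recorded at visits and in weekly calls, so where removal follows a recorded low rating, it depends on observed data. This stands: one might infer that the design makes the data missing not at random, and the article does not show that. But {20c} does not commit to using mood in the imputation; {20b} mentions it only as a possible mediator.
- **A third of the effect lost is a bound.** It makes all 24 budgeted losses patients with the largest worsening. Losses also include withdrawn consent, adverse reactions and an offered therapy place, and removal needs a drastic or marked increase. A cut-off of 0.66 SD is hardly that. This stands; no share is given, so only the range may be quoted.
- **The bias works against the trial's hypothesis.** True in this scenario. One might infer that the plan favours a positive finding; the calculation does not show that for a single fixed method. If removal differed between arms for other reasons, bias could go either way.
- **No proven conflict with intention-to-treat, and raters stay blind.** One might read {17b} as contradicting {20c}, or as unblinding the MADRS rater. Nothing says the t6 rating is refused after stopping, {17b} does not say who is unblinded, and {17a} and the Strengths section keep outcome raters separate and blinded. These are ambiguities, and the unblinding one is secondary.

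Imputation detail may properly sit in an analysis plan. The rule that sensitivity results help choose the method is in the article, however, and no part of this defence answers it.

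**Conclusion.** The concern holds in a limited form. Section {20c} makes the missing-data strategy depend on its observed impact and on an assumption that observed data cannot confirm, with no fallback. Some missing t6 MADRS values will be related to the outcome, and the article leaves open whether ratings continue after discontinuation.

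For a true difference of 0.40 SD, r = 0.5 and 5 to 20% removed for worsening, a baseline-only MAR analysis gives about 0.35 to 0.26 SD. With mood ratings in the model, the result lies between about 0.30 and 0.40 SD, depending on the removal share and on whether removal follows the recorded rating. There is no bias under no effect with equal removal. The removal share and both correlations are assumptions, and the 20% case is an upper bound rather than a forecast. The change should be made before the data are analysed; the point does not invalidate the design.

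**What to change.** 1. In {20c}, name one primary method that does not depend on the sensitivity results: multiple imputation under MAR, by arm, with baseline MADRS, BDI-II and the weekly mood ratings as auxiliary variables.
2. Use sensitivity analyses only to test robustness. Include delta-adjusted imputation for patients who left because of worsening or adverse reactions, identified from the discontinuation form in {18b}.
3. Reconcile {11b}, {17b} and {20c} by separating stopping treatment from leaving the study. Attempt the scheduled t6 MADRS in every patient who stopped treatment without withdrawing consent.
4. State in {17b} that unblinding does not extend to the MADRS rater.

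The clinical stopping criteria stay as they are. The cost is a few sentences of text, slightly more analysis work and some extra attempted t6 visits; no new instrument or visit type is needed.

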### Plans to give access to the full protocol, participant-level data, and statistical code {31c}

The full protocol and statistical codes are provided on request. Participant-level datasets will be provided to experts on request after thorough clearing to ensure privacy of participants.

## Oversight and monitoring

### Composition of the coordinating center and trial steering committee {5d}

This trial has been approved by the Ethics Committee of the medical chamber of the state of Hessen, Germany (Ethik-Kommission der Landesärztekammer Hessen; reference number: 2019–1349-evBO). The coordinating center for clinical studies at the University of Marburg coordinates this clinical trial locally. The steering committee is comprised of the principal investigators of the Collaborative Research Centre 289-Treatment Expectation (https://treatment-expectation.de/en/projects-people/research-projects; https://gepris.dfg.de/gepris/projekt/422744262).

### Composition of the data monitoring committee, its role and reporting structure {21a}

The data monitoring committee has been established 2021 and consists of external clinician-scientists and psychometricians, all of whom have no affiliation with the trial or the funding body. The committee meets once every 6 months to oversee the procedures and highlight any changes that might need to be made to ensure data quality and participant safety on an ongoing basis.

### Adverse event reporting and harms {22}

No harm is expected from participation in the trial. There are no known side effects for emotional writing. Buscopan can produce some side effects in rare cases (1 in 100 may experience dry mouth, constipation, blurred vision, fast heart rate; very rare: painful red eye and loss of vision, difficulty urinating). Generally, participation in a clinical trial can be distressing and may lead to temporary changes in mood and depressive symptoms. All participants, including control group participants, are contacted weekly to monitor changes in mood and experience of side effects. In case a participant is reporting adverse events, such as a drastic increase in negative mood, suicidal ideation, or other unintended effects, participants will be referred to senior clinicians at the outpatient clinic to ensure safety. Data about adverse events and drop-outs will be reported to the data monitoring committee on an ongoing basis. Side effects will be monitored with the GASE (see above).

### Frequency and plans for auditing trial conduct {23}

External auditing is done by the data monitoring committee on a 6 monthly basis. In terms of internal auditing, weekly meetings with the research staff are held to plan and schedule the workload and discuss possible issues related to the participants progressing through the trial. Monthly graphs depicting participants’ inclusion status and ongoing recruitment strategies are also discussed.

### Plans for communicating important protocol amendments to relevant parties (e.g., trial participants, ethical committees) {25}

Any necessary protocol modifications will be submitted to the overseeing ethics committee for approval. Protocol changes will also be published in the preregistration of this study (registered at www.clinicaltrials.gov; ID: NCT04719663).

### Dissemination plans {31a}

The results of this clinical trial are planned to be published in scientific journals in the field of clinical psychology, psychiatry, and clinical practice. Furthermore, the results will be disseminated to the public through the science communications platforms of the CRC (e.g., website, Twitter, YouTube). Scientific talks and presentations for researchers, healthcare practitioners, and/or the public present another forum for dissemination of the results.

## Discussion

Studies and clinical trials on anti-depressant treatments have shown that placebo arms reveal impressive results rivaling those found in the verum arms [2, 4, 5, 78]. It is yet unknown whether treatment effects can be disentangled from placebo effects and what role common treatment factors, such as pre-treatment expectations, play in producing treatment effects. In this trial, we assess the ways in which clinician-patient communication may help to optimize treatment expectations in the treatment of depression. Specifically, this trial assesses the effects of congruent vs. incongruent illness rationales on treatment effects of two active placebo treatments for major depression with the aim of improving treatment effects.

We hypothesize that illness rationales that are congruent with the subsequent placebo treatment will show larger treatment effects (reduction of depressive symptoms) than illness rationales that are incongruent with the subsequent placebo treatment. Specifically, a psychological causal explanation of depression leads to a better outcome than a biological explanation if a psychological active placebo intervention is provided. Biological causal explanations of depression lead to a better outcome than psychological explanations if an active placebo intervention is provided as treatment. We further hypothesize that the mechanism by which treatment-congruent illness explanations lead to better outcomes is through a modification in the patients’ treatment outcome expectations. Biological rationales increase the expectations for the outcome of pharmacological treatments, while psychological rationales increase positive outcome expectation for psychological interventions. Finally, we hypothesize that inter-individual differences in the effect are associated with pre-treatment experiences and expectations, depression severity, and comorbid anxiety.

Common treatment factors, such as outcome expectations, credibility perceptions, and the therapeutic alliance, have been shown to affect treatment success in pharmacological and psychological trials [28, 30, 31]. We chose to focus on the clinician-patient communication, because the clinician-patient interactions are an integral part of common healthcare procedures and are therefore likely to affect common treatment factors [79, 80]. Yet, little is known about the communicative devices that may work to enhance treatment responses.

Recent experimental research suggests that a therapist’s display of warmth and competence can influence treatment expectations in a therapeutic setting, with participants reporting higher expectations for improvement when therapists display both warmth and competence [81]. These findings highlight the importance of considering therapist behavior and characteristics in shaping patient expectations in therapy.

Furthermore, research on placebo interventions has shown that a convincing treatment rationale which considers patients’ expectations, hopes, and learning history that is delivered by a trustworthy and credible clinician who believes in the remedial qualities of the intervention is able to produce similar treatment effects as other evidence-based interventions [12, 79, 82–85]. We believe a treatment rationale that is in line with the illness model will produce more fruitful grounds for a patient to expect and experience a positive treatment response, irrespective of what the treatment might be (pharmacological or psychological).

Leading up to the current trial, we conducted a pilot study, in which the illness rationales were provided via an animated video. The results showed that both illness explanations (biological vs. psychological causes) were rated similarly in terms of credibility. This is perhaps reflective of the observation that the narrative around illness explanations for depression in the media and in medical practice seems to occur along the biological vs. psychological divide and rarely encompass a bio-psycho-social illness explanation [34]. In contrast to the pilot, in which the credibility of the illness rationale itself was tested, this trial utilizes illness and treatment rationales that are provided face-to-face by clinicians, in order to create a more externally valid context. Moreover, we measure the perceived warmth and competence of clinicians and research staff during key interactions, providing additional insight into the underlying mechanisms of expectation change emerging from the research on common treatment factors.

### Design

Using the BDI-II as a secondary outcome measure for subjective depressive symptoms will further shed light on possible disparities between expert-rated depressive symptoms and the subjective experience of depressive symptoms, which have previously been observed in meta-analytic studies [5]. With other secondary outcomes, such as state anxiety and perceived stress, we are able to assess how expectation modulation and the subsequent interventions aimed at treating depressive symptoms may also interact with related processes (e.g., stress management) and symptoms (e.g., anxiety).

Moderator analyses will explore whether customized approaches in communication could provide an added benefit, for example, for people with high levels of trait anxiety or those with negative previous treatment experiences. Mediator analyses will provide insights into the processes and mechanisms (e.g., expectation updating) by which communication might be able to alter the strength of the placebo response in the treatment of depression.

### Strengths

This trial has several strengths in terms of design and methodology. We intend to investigate and modulate placebo mechanisms directly, using a highly ecological study design with clear implications for clinical work. Few studies in the placebo field account for the natural variation of symptoms [10]. Thus, the inclusion of the natural course control group will allow us to observe whether changes in depressive status could be due to regression to the mean. Based on ethical considerations, this group is kept comparatively small (1/5 of the anticipated sample) in order to give more participants the chance to receive an active placebo treatment. The exclusion criteria are kept to a minimum in order to preserve external validity.

Furthermore, the trial has a 2 × 2 balanced design in the intervention conditions; the chances of being randomized in one of the four treatment arms are equal. This is important as treatment expectations can already be influenced by unequal chances (and thereby unequal prospects for the participant) of being randomized into the different conditions [86].

The blinding procedure presents another strength of this trial, albeit demanding logistically. The separation of outcome raters and clinicians who deliver the rationales for each participant ensures blinding of the outcome (MADRS) raters throughout the trial. Furthermore, clinicians who deliver the illness rationale are blinded to the treatment condition at the time they deliver the illness rationale to the patients. This blinding procedure ensures that there is no knowledge of whether a congruent or incongruent treatment will follow, to avoid bias in the clinician’s delivery of the illness rationale. In addition, the research staff that deliver the interventions after the rationale are different members of staff than the outcome assessors and the clinicians who provide the rationale. This ensures their blinding to the congruency condition, minimizing potential biases in the delivery of the placebo interventions.

